**Conclusions:**

To our knowledge, this study is the first clinical trial to compare the cost- effectiveness of PAiT to standard 10 Hz rTMS as treatment for patients with TRD. The results of our study will offer professionals evidence from a sufficiently powered trial to determine whether the PAiT protocol is more effective than standard high-frequency rTMS. Specifically, it will assess whether PAiT leads to a shorter treatment duration for depression and greater societal or occupational participation among patients with TRD. In addition, this trial will provide further insights into the underlying mechanisms related to treatment effect, the effects of rTMS or accelerated intermittent theta-burst stimulation on cognitive domains such as executive functioning and emotion, possible differences in side effects, long-term effects, and factors contributing to possible relapse.

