### Durability of the Effects of Personalized aiTBS

As of 2024, little was known about the long-term effects of personalized aiTBS. One could argue that the same remission or relapse course can be expected as for ECT, that is, quick antidepressant effects directly after the intensive 5-day treatment in combination with a high chance of relapse in the following weeks. Therefore, our study will have weekly clinical assessments for 7 weeks in both conditions to enable comparisons in treatment efficacy, during treatment, directly after treatment, and 1 week after treatment between rTMS and PAiT, along with follow-up clinical assessments at 6 and 25 weeks after treatment. In addition, we will investigate the (factors contributing to) side effects during the treatment in both conditions using an in-house questionnaire [17].

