### Study Design

This multicenter single‐blind RCT consists of 2 phases in which participants will be randomly assigned to either standard 10 Hz rTMS (30 daily rTMS sessions in 6 weeks, providing a total of 90,000 magnetic pulses) or PAiT (50 iTBS sessions in 5 days, providing a total of 90,000 pulses) [11,12], with 4 follow‐up moments at 7, 12, 26, and 31 weeks after baseline. In either condition, the timing of these measurements translates to clinically relevant time points at 6 and 25 weeks after treatment, as well as aligned postbaseline follow-ups that are important for the cost-effectiveness analysis. As such, the follow-up measurement at 31 weeks after baseline is only used in the rTMS condition (25 weeks after treatment).

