### Statistical Analyses

#### Overview

Statistical analyses will be performed on the intention‐to‐treat as well as the per protocol sample. Missing data will be replaced using the multiple imputation method. For all analyses, corrected *P* values of <.05 will be regarded as statistically significant. Safety data (eg, side effects) will be collected and summarized in the study results. A description of the analyses for the primary, secondary, and exploratory objectives is provided in the following sections.

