For the Percentual reduction of depressive symptoms, as measured with self‐rated PHQ-9 on each day using the PAiT protocol, compared to weekly reduction of depressive symptoms, as measured with PHQ-9 during standard 10 Hz rTMS we will use linear mixed models. Similarly, we will determine percent reduction of depressive symptoms, as measured with the clinically assessed HDRS‐17 before, during, and after treatment, as well as at the follow-up moments.

Relapse, at 6 and 25 weeks after treatment, defined as (1) sustained remission, that is, HDRS-17≤7, and (2) sustained response, that is, response at end of treatment maintained through week 6 and 25. During treatment phase (T2), we will conduct the HDRS-17 weekly for 6 weeks for both treatment arms. By doing this, using the chi-square test, we can compare the remission rate with PAiT after 6 weeks to 6 weeks of treatment with standard 10 Hz rTMS; this is of interest as patients allocated to PAiT only receive treatment for 1 week.

We will report the prevalence of side effects during and directly after treatment based on international recommendation [17]. We will establish the tolerability and side effects of PAiT and rTMS. We will use qualitative data collected while supporting the implementation of PAiT, to analyze health care system–, patient‐, and clinician‐related factors that influence the implementation of PAiT in clinical settings. We will use a 1-tailed paired *t* test or an ANOVA to compare patient-reported changes in mood 1 week after treatment (as measured with self-rated PHQ-9) with clinician-reported clinical impression (as measured with the Clinical Global Impression scale).

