### Relevance for Practice

PAiT can be applied in various treatment settings and by various health care professionals. If positive, the results of our study will provide Dutch and international professionals with an adequately powered trial answering whether PAiT is an evidence‐based therapy for depression. A novel therapy is necessary to overcome TRD in patients who did not respond after 2 or more evidence‐based treatments. In addition, this trial will provide further insights into the differences in the side effects, long-term effects, and (factors contributing to) possible relapse between rTMS and PAiT.

Different rTMS equipment will be used at different sites in this trial. Technical and practical differences in the equipment may introduce variability across sites. However, using different machines is important for generalizability of the results because, in daily practice, mental health institutions use different rTMS machines. To minimize variability in the practical application of rTMS, we thoroughly instruct technicians to follow our provided training and standard operating procedures. All treatments will be conducted using neuronavigation systems with a calibration accuracy of less than 3 mm. In addition, we will control for rTMS machine or site to ensure the reliability of our analyses and investigate the impact of different equipment.

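### Side-effect prevalence is tied to treatment courses of 5 days and 6 weeks, so the two arms' figures cannot be compared on their own in either direction

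*Protocol article*

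**What the plan says.** In the protocol article, Secondary Study Parameters gives the measure and its window: "We will report the prevalence of side effects during and directly after treatment". It adds "We will establish the tolerability and side effects of PAiT and rTMS". The Overview of the statistical analyses says "Safety data (eg, side effects) will be collected and summarized in the study results". The introduction's section on durability describes the collection in the same terms: "side effects during the treatment in both conditions using an in-house questionnaire".

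Study Design sets the two courses. PAiT is "50 iTBS sessions in 5 days, providing a total of 90,000 pulses"; the comparator is "30 daily rTMS sessions in 6 weeks, providing a total of 90,000 magnetic pulses".

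Several places show that the side-effect results are meant to be read between arms. The section on the study's contribution to the field gives the safety of PAiT versus rTMS as a reason for the trial. Secondary Outcomes lists tolerability and side effects fifth. The abstract's Conclusions promise insight into "possible differences in side effects, long-term effects, and factors contributing to possible relapse", and Relevance for Practice promises "further insights into the differences in the side effects" between rTMS and PAiT.

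The section on challenges says both arms have weekly clinical measurements for 7 weeks from the start of treatment. Secondary Study Parameters uses weekly HDRS-17 ratings in both arms to compare remission at 6 weeks. It gives no matching comparison for side effects.

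**The concern.** A prevalence needs a window. Here the window is the treatment course, and the courses differ about sixfold in calendar time and treatment days (5 versus 30). They also differ in session count, but the other way (50 versus 30). Complaints that begin in PAiT patients in weeks 2 to 6 lie largely outside the stated window, apart from whatever counts as directly after treatment. The same weeks count in full for rTMS.

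The article does not say whether prevalence means any occurrence over the course, the proportion affected at an assessment, or the proportion of sessions with a complaint. The three respond differently to the length and intensity of a course.

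At stake is what the trial will say about relative tolerability. Two prevalences printed side by side will be read as a comparison, although part of the gap, or all of it, may come from the window and the number of sessions.

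**Working it through.** The article gives no side-effect rate, so there is no figure of its own to reproduce. The check asks how far apart the two prevalences could be if the arms did not differ.

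**Inputs from the article.** PAiT: 5 treatment days, 50 sessions (Study Design). rTMS: 6 weeks, 30 daily sessions, so 30 treatment days (Study Design). Clinical assessments during treatment: daily in PAiT, weekly in rTMS (Table 1), so about 5 and 6 occasions.

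**Assumptions.** Prevalence means any occurrence. The risk p per unit of exposure is the same in both arms and independent across units. The values of p are illustrative; none comes from the article.

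**Formula.** Prevalence = 1 − (1 − p)^k, where k is the number of units in the course.

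| Unit on which risk is equal | p | PAiT | rTMS |
|---|---|---|---|
| Treatment day (k = 5 vs 30) | 2% | 1 − 0.98^5 = 9.6% | 1 − 0.98^30 = 45.5% |
| Treatment day | 5% | 1 − 0.95^5 = 22.6% | 1 − 0.95^30 = 78.5% |
| Calendar week (k = 1 vs 6) | 10% | 10.0% | 1 − 0.90^6 = 46.9% |
| Session (k = 50 vs 30) | 0.5% | 1 − 0.995^50 = 22.2% | 1 − 0.995^30 = 14.0% |
| Session | 1% | 1 − 0.99^50 = 39.5% | 1 − 0.99^30 = 26.0% |
| Session | 2% | 1 − 0.98^50 = 63.6% | 1 − 0.98^30 = 45.5% |
| Assessment (k = 5 vs 6) | 10% | 1 − 0.90^5 = 41.0% | 1 − 0.90^6 = 46.9% |

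Equal risk per treatment day puts PAiT 36 to 56 points lower (45.5 − 9.6 = 35.9; 78.5 − 22.6 = 55.9). Equal risk per session puts PAiT 8 to 18 points higher (22.2 − 14.0 = 8.2; 63.6 − 45.5 = 18.1). Equal detection per assessment leaves the arms about 6 points apart. The article allows PAiT patients to miss up to 10 of 50 sessions; with 40 delivered at 1% per session, PAiT is 1 − 0.99^40 = 33.1%, still above 26.0%.

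**What a common window changes.** For background complaints at 10% per week, a 7-week window gives 1 − 0.90^7 = 52.2% in both arms, in place of 10.0% versus 46.9%. For complaints caused by treatment days, the window changes nothing: treatment days remain 5 versus 30, and 22.6% versus 78.5% stands.

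**No single denominator is neutral.** If the risk per treatment day is 5% in both arms, complaints per session are 5%/10 = 0.5% in PAiT and 5%/1 = 5% in rTMS. Both rates are needed to show what kind of difference is present.

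**The case against.** A reader might infer that the stated window makes PAiT look better tolerated. The documents do not support that. It requires any-occurrence prevalence and a risk that accrues by calendar time or treatment day, and the article states neither. The side effects it names, headache and scalp pain, are described as transient and linked to stimulation. Risk could therefore accrue per session, which reverses the sign. If side effects follow the Table 1 schedule, daily assessment in PAiT against weekly in rTMS also alters detection.

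The objection goes further. The article speaks of reporting and summarizing and states no between-arm test of side effects. Prevalence over a whole course is a legitimate patient-level summary, because fewer treatment days is a real feature of PAiT. Complaints recur in the same patients, so independence across days or sessions overstates the gaps. The questionnaire's schedule, recall period and scoring are not shown and may sit in the full protocol or analysis plan; it may already be given at the weekly visits.

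All of this stands against a directional claim and against treating any tabulated figure as an estimate of bias. It does not remove the narrower point. The window is stated in the article, and the article says that differences in side effects between the arms will be drawn from the trial. On that window the two figures do not answer that question.

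**Conclusion.** The point holds in limited form. Side-effect prevalence is tied to courses that differ in length and, in the opposite direction, in session count, while the article intends conclusions about differences between arms. With no true difference on a given risk scale, the prevalences can lie tens of points apart either way: about 23% versus 79% (PAiT versus rTMS) at 5% per treatment day, about 40% versus 26% at 1% per session. These figures rest on assumed, equal and independent risks and on reading prevalence as any occurrence. They show that the contrast cannot be interpreted on its own. They establish neither the direction nor the size of a bias. The point is minor and concerns a descriptive secondary outcome.

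**What to change.** Keep prevalence over each arm's course, labelled as a patient-level summary of a complete course, and say whether it means any occurrence. Add two things beside it:

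1. Side-effect rates per session delivered and per treatment day, by arm.
2. Prevalence from baseline to week 7 in both arms, using the weekly visits already planned for both. State that this window equalizes observation of background complaints but not treatment exposure.

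The cost is small: a short questionnaire at existing PAiT visits in weeks 2 to 7, if it is not already given there, and a few lines of analysis text. With 31 of 108 patients enrolled by December 2024, common-window data may be incomplete for those already past week 7. For them, the per-session and per-day rates can be reported where the data collected allow, and the number of patients behind each figure should be shown.

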### Study Procedures

Study information is provided to eligible participants, and these patients are contacted again after at least 7 days to discuss participation and any remaining questions. If patients choose to participate, they will be invited to a research intake session, during which they will sign the informed consent form and undergo screening for inclusion and exclusion criteria. Participation is voluntary, and individuals may withdraw from the study at any time. Table 1 shows an overview of the study. Participants who were allocated to standard 10 Hz rTMS will be offered PAiT after the end of the study (eg, 25 weeks after the last rTMS session). We will request patients allocated to PAiT to postpone enrolling in standard 10 Hz rTMS for 25 weeks after the last treatment session. This is merely a request as patients are allowed to ask for treatment as usual, including standard 10 Hz rTMS. Our participating treatment centers deem it not ethical to withhold this usual 10 Hz rTMS treatment upon a patient’s request. In addition to clinical effectiveness, we will study patient‐reported outcomes, tolerability, and safety. Alongside this RCT, we will also conduct an economic evaluation and evaluate facilitating and hindering factors related to implementation in the group of researchers and health care professionals involved in this study. The funding agency, the Efficiency Studies arm of the Care Research Netherlands and Medical Sciences of the Dutch Research Council, has explicitly requested that the trial be based in care as usual.

**Table 1 table1:** An overview of the study for both treatment conditions.

			rTMS^a^		PAiT^b^
**T0**					
	Week –2	Screening: clinicometrics; biobank; MRIc pre+additional tasks; rTMS premeasurements		Screening: clinicometrics; biobank; MRI pre+additional tasks; PAiT premeasurements	
**T1**					
	Week 0	Baseline		Baseline	
**T2**					
	Week 1	Treatment Clinicometrics (weekly)		Treatment Clinicometrics (daily)	
	Week 2	Biobank		Follow-up (1 week): clinicometrics (weekly); MRI post+additional tasks; biobank	
	Week 6	Clinicometrics		Clinicometrics	
**T3**					

	Week 7	Follow-up: clinicometrics; MRI post+additional tasks; biobank		Follow-up: clinicometrics; biobank	
**T4**					
	Week 12	Follow-up: clinicometrics; biobank		Follow-up: clinicometrics	
**T5**					
	Week 26	Follow-up: clinicometrics		Follow-up (25 weeks): clinicometrics	
**T6**					
	Week 31	Follow-up (25 weeks): clinicometrics		Clinicometrics	

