#### Secondary Outcomes

In addition to the primary outcomes, secondary outcomes will be assessed to provide a more comprehensive understanding of the effectiveness and impact of rTMS/PAiT. First, an economic evaluation based on the general principles of a cost‐effectiveness (utility) analysis, which will be performed alongside the intervention by comparing patients treated with PAiT with those receiving standard 10 Hz rTMS. In addition, societal costs and health consumption will be assessed for the economic evaluation at baseline and 7, 12, and 26 weeks after baseline. We will use health‐related quality of life determined with the EQ‐5D‐5L and health care use or costs, patients’ and their family’s out‐of‐pocket costs, and productivity losses owing to absenteeism measured with the Trimbos Institute and Institute for Medical Technology Assessment Cost questionnaire for Psychiatry [24]. Second, patient‐reported outcome measures will be recorded, that is, positive mental health, as measured with Mental Health Continuum‐Short Form [25] and subjective memory loss. Third, percentage reduction of depressive symptoms will be measured with self‐rated 9-item Patient Health Questionnaire (PHQ-9) on each treatment day and the HDRS‐17. Fourth, relapse will be measured at 6 and 25 weeks after treatment. Relapse was defined as an HDRS‐17 total score of ≥15 for 2 consecutive assessments separated by 5 to 15 days or hospitalization for depression. Fifth, we establish tolerability of the treatment and side effects of PAiT and rTMS [9]. Sixth, we will identify health care system–, clinician‐, and patient‐related factors that influence the implementation of PAiT were identified to inform the development of an implementation plan. Seventh, we will compare patient-reported changes in mood 1 week after treatment (as measured with self-rated PHQ-9) with clinician-reported clinical impression (as measured with Clinical Global Impression [23]).

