### Challenges of the Proposed Trial

We anticipate that patients are drawn toward our trial because the 1-week intensive treatment is appealing to them. However, these patients may not be willing to be randomized. We aim to tackle this by offering PAiT after the end of the study participation (eg, 25 weeks after the last rTMS session) to patients who are randomized to the 6-week rTMS arm. To date, the PAiT protocol, modeled after the SNT protocol for TRD, is only offered in the Netherlands in our trial.

Another challenge is that the PAiT protocol with 10 sessions on 5 consecutive days is intense, and it is anticipated that patients may miss sessions due to various reasons (eg, traffic or oversleeping). In a complete course, participants can miss 20% (10/50) of sessions at maximum. If >20% (10/50) of sessions are missed, it is considered a failed course. In the rTMS condition, depending on feasibility for the patient and the rTMS team, a maximum of 6 missed sessions may be added to the end of the course. In the PAiT condition, in concordance with the Stanford group, missed sessions will not be rescheduled. If optimal adherence to the protocol is not possible for a patient due to limited traveling capacity or due to the distance from the treatment center, we offer admission to the ward.

To further facilitate tolerability of the PAiT condition, separate rooms will be provided for the patients to rest in between sessions.

This clinical trial includes a direct comparison between treatments of varying durations. This poses the challenge of establishing a representative time point for measuring the primary outcome. To capture the clinical effects in more detail and over time, we will perform weekly clinical measurements for 7 weeks following the start of the treatment regardless of the treatment condition. The time point of measuring the primary outcome was set to 7 days following the final treatment session.

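### The planned paired t test of PHQ-9 change against the Clinical Global Impression cannot measure patient-clinician agreement, and the PHQ-9 schedule is stated in two ways

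*Protocol article*

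**What the plan says.** Secondary Outcomes sets the question: "we will compare patient-reported changes in mood 1 week after treatment" on the self-rated PHQ-9 with the clinician's CGI rating. Secondary Study Parameters fixes the method: "We will use a 1-tailed paired *t* test or an ANOVA to compare patient-reported changes in mood 1 week after treatment" with "clinician-reported clinical impression (as measured with the Clinical Global Impression scale". It gives no common unit, no direction for the single tail and no rule for choosing between the t test and the ANOVA. The Overview of Statistical Analyses applies a corrected 5% significance threshold to every analysis, this one included.

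On when PHQ-9 is taken, the sections differ:
- Secondary Outcomes: "Patient Health Questionnaire (PHQ-9) on each treatment day", with no distinction between arms.
- Secondary Study Parameters: daily under PAiT, "compared to weekly reduction of depressive symptoms, as measured with PHQ-9 during standard 10 Hz rTMS we will use linear mixed models".
- Table 1 (Study Procedures): "Treatment Clinicometrics (daily" for PAiT in week 1 and weekly for rTMS, without naming the instruments.
- Challenges of the Proposed Trial: "we will perform weekly clinical measurements for 7 weeks following the start of the treatment regardless of the treatment condition", again without naming PHQ-9.

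**The concern.** A paired t test asks whether the mean within-patient difference is zero, so both members of the pair must be in one unit. Here one member is a change in a nine-item sum score and the other is a global rating. Zero difference between them does not correspond to agreement, and a non-zero difference does not correspond to disagreement. The result would still be reported against the 5% threshold and could be read as evidence that patients and clinicians do, or do not, see the same change.

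The schedule mismatch affects which data are collected. Over 30 rTMS sessions at one per day, one reading gives about 30 PHQ-9 assessments per rTMS patient during treatment, and the other gives about 6.

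**Working it through.** **The plan's own figure.** The protocol gives no figure for this analysis. Its only relevant design figure is the sample size, used below as an input. With 55% vs 25%, two-sided 5% and 80% power (pooled variance, no continuity correction):

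n per arm = [1.96·√(2·0.40·0.60) + 0.842·√(0.55·0.45 + 0.25·0.75)]² / 0.30² = (1.358 + 0.555)² / 0.09 ≈ 40.7, rounded up to 41.

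This gives 82 in total, and 82 × 1.32 = 108.24, so both 82 and 108 reproduce.

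**Inputs for the paired test.** n = 82 is from the protocol. The rest are assumptions, because the documents give none: mean PHQ-9 reduction m (8 as the base case), SD 6; CGI mean 2.5, SD 1.2, on a 1-to-7 scale. The protocol does not state the scoring direction of the CGI, so the correlation r is taken with either sign.

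**Formula.** Variance of the paired difference = 6² + 1.2² − 2·r·6·1.2 = 37.44 − 14.4r. Expected t ≈ (m − 2.5)·√82 / √(37.44 − 14.4r).

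**Base case, m = 8.** The numerator is 5.5 × 9.055 = 49.8.

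| r | √(37.44 − 14.4r) | expected t |
|---|---|---|
| −0.99 | 7.19 | 6.9 |
| 0 | 6.12 | 8.1 |
| +0.5 | 5.50 | 9.1 |
| +0.99 | 4.82 | 10.3 |

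The test is far into the rejection region whether the two ratings are unrelated or almost perfectly related.

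**Varying the mean and the tail.** One-tailed rejection at 5% was simulated with the same SDs, rounded scores, correlations 0, 0.5 and 1, n = 82 and 108, and 2,000 runs per setting. Ranges are across all correlations and both sample sizes.

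| mean PHQ-9 reduction | tail: PHQ-9 above CGI | tail: PHQ-9 below CGI |
|---|---|---|
| 0 | 0% | 98–100% |
| 2.5 | 3–5% | 5–7% |
| 5 | 98–100% | 0% |
| 8 | 100% | 0% |

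Across the rows the result swings from 0% to 100% with the mean and the tail. Within a row it barely moves between correlation 0 and correlation 1. At m = 2.5 the numerator is zero, so the test rejects at about its nominal 5% even if the two ratings agree perfectly.

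**Standardizing does not rescue it.** If each measure is converted to z-scores, both means are 0 and the paired difference is 0 by construction.

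**The ANOVA alternative.** Two readings are possible. If the instrument is the within-patient factor with two levels, F = t² and the same fault remains. If PHQ-9 change is compared across CGI categories, no common unit is needed and the analysis is valid. The text does not say which is meant.

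**The case against.** The strongest defense is that this is one secondary outcome among seven, that one reading of the ANOVA is sound, and that an analysis plan not shown may settle the details. The first two points stand and limit the severity. The third does not remove the problem: the paired t test and its single tail are stated in the protocol, so this is a named method that does not fit the question, not an omitted detail.

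Three stronger readings are tempting, and the documents do not support them.

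- *The test will always be significant.* The table above shows otherwise: rejection depends on the means and the tail. The supportable statement is that the test is insensitive to agreement.
- *The daily PAiT and weekly rTMS series have no common scale, so that mixed model is invalid.* Both arms use PHQ-9 percent reduction, and a mixed model accepts unequal visit times. The time coding does matter. With an equal end-of-course reduction (assumed 50%, 41 per arm), a simulated slope comparison rejects in 100% of runs on calendar days and 5.5% on fraction of course. But the protocol does not fix a wrong coding, the choice is commonly left to the analysis plan, and weekly measurements are planned in both arms.
- *Percent reduction is itself an error.* Under assumed inputs it costs between 0.3 and 5.7 points of power against a baseline-adjusted raw score. That is a small matter of efficiency on unpowered secondary outcomes.

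**Conclusion.** The paired t test is wrong as written. It compares two instruments without a common unit, in an unstated direction, and its P value says nothing about patient-clinician agreement. The figures (t of 6.9 to 10.3; about 5% rejection at a mean reduction of 2.5) rest on assumed means and SDs. The insensitivity to correlation does not depend on those particular values, because agreement enters only through the variance of the difference and never through the null hypothesis.

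The PHQ-9 schedule also contradicts itself for rTMS: Secondary Outcomes implies each treatment day in both arms, whereas Secondary Study Parameters says weekly and Table 1 is consistent with that. Severity is minor. The chi-square test of remission and the sample size are untouched.

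**What to change.** 1. Remove the paired t test. Report the Spearman correlation of PHQ-9 change with CGI, two-sided, with a 95% CI. Add a regression (or ANOVA) of PHQ-9 change on CGI category with arm and the arm-by-CGI interaction, to show whether the relation differs between unblinded treatments. This uses data already planned and costs only wording.
2. Reconcile Secondary Outcomes with Secondary Study Parameters and Table 1 on how often PHQ-9 is taken during rTMS.
3. Base the between-arm PHQ-9 comparison on the weekly assessments common to both arms, and present the daily PAiT scores descriptively. First confirm that those weekly assessments include PHQ-9 in the PAiT arm after week 1, since the text names only HDRS-17 as weekly in both arms. If they do, the change is wording. If they do not, it is a change to data collection in a trial that had already enrolled 31 patients by December 2024, so it should be settled early.
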